### Possible risks to participants

This study involves greater than minimal risk with the potential for direct benefit. In conventional heart transplantation, the most serious risks are graft failure, cardiac allograft vasculopathy, infection and acute rejection, which altogether account for the majority of deaths after conventional heart transplantation. The relative importance of these causes of death vary over time post-transplant. Risks of partial heart transplantation are expected to be similar to the risks of standard valve replacement but less than the risks of conventional heart transplant. A complete list of risks is provided in S2 Appendix.

The most serious risks are scheduling issues related to donor heart availability and rejection of the transplanted valve. The risk of rejection is theoretically lower compared to a full heart transplant. The risk of death during and after the operation is similar to the risks for standard valve replacement with a homograft. There is no risk of disease developing in the blood vessels that supply the heart (i.e., coronary arteries) and no risk of heart muscle dysfunction given that these tissues are not being transplanted.The surgery will result in a permanent scar in the middle of the chest. This is the same scar that would result from a standard valve replacement or full heart transplant. This scar may require medical follow-up after surgery and may temporarily restrict the subject from exercise and/or sports participation in the future.Open heart surgery involves the risk of death, brain damage, or other organ damage such as kidney injury.The need for blood transfusion during surgery poses a risk of infection from the blood or a reaction to the blood. The risk of infection from transfused blood is extremely low given current screening processes.Patients receiving a partial heart transplant may also become sensitized to the transplanted valve tissue. This will decrease the donor pool if the patient ever requires a heart transplant.There is a risk of loss of confidentiality.There may also be additional risks that are currently unknown.

### Possible benefits to participants

The possible benefits to participants may include the need for fewer valve replacement operations and their substantial morbidity and mortality during childhood.

The most important advantage of partial heart transplantation is growth of the transplanted valve. This minimizes the morbidity and mortality from successive implant exchanges.Avoiding reoperations will improve neurodevelopmental outcomes as repeat cardiac operations are associated with worse neurodevelopmental outcomes [21].Avoiding reoperations will decrease psychological and financial stress for subjects’ caregivers and families [22].The transplanted valve would be durable without the need for anticoagulation.The transplanted valve may have better valve function with more favorable loading conditions on the ventricular myocardium.Because of fewer surgeries and their risks, the subjects may potentially have longer lifespans.

### Data analysis

Data will be exported from the study database for statistical analysis. Given the goal sample size of five participants and lack of control group, simple descriptive statistics will be used.

### Confidentiality provisions

All completed CRFs will remain confidential and will be stored in locked cabinets within the locked offices of the study investigators at MUSC, accessible only to study team members. Study data will reside in password-protected computers within locked offices of study investigators at MUSC, accessible only to study team members. All data stored on MUSC servers are password-protected and backed up nightly. The network is protected on multiple levels that include firewalls, intrusion detection software, and continuous monitoring by the Information Services Security Department.

The study investigators will be primarily responsible for monitoring all study patients for the occurrence of adverse events and unanticipated problems as outlined above.

A DSMB will be chaired by a physician and will be used to monitor the progress of this clinical trial and review safety and effectiveness data while the trial is ongoing. DSMB members will be comprised of senior faculty from other institutions, and will include a pediatric transplant cardiologist, a pediatric cardiac intensivist, and a pediatric cardiac surgeon. None of these individuals will be directly involved with the undertaking of this study or affiliated with MUSC.

The DSMB will be responsible for reviewing the research protocol (and any amendments thereof) and the informed consent documents (S3 Appendix) prior to the onset of patient recruitment. The DSMB will meet virtually one month after each of the first three patients are enrolled and annually thereafter to review study data. The study investigators will prepare interim reports, including a summary of outcomes and adverse events, for DSMB review.

The DSMB will consider and review the following: major protocol modifications proposed by the study team; participant recruitment, accrual and retention; confidentiality issues; factors external to the study when relevant, such as scientific or therapeutic developments that may have an impact on the safety of the subjects or the ethics of the trial; and investigator-assigned relationships between the intervention and adverse events. Following each meeting, the DSMB will prepare a written report on the safety and scientific progress of the trial and make recommendations to the study investigators concerning continuation, termination or modification of the trial based on the observed beneficial or adverse effects of the research. The DSMB will also meet at the conclusion of the study, and as needed to review serious adverse events.

A subject will be removed from the study if a parent or legal guardian withdraws consent, or if one of the patient’s primary attending physicians elects to remove the patient from the study. Additionally, all clinicians who are uninvolved with the trial but participate in the care of the subjects will be encouraged to report adverse events to the study investigators. The study investigators will meet every six months to review adverse events and to assess the risk/benefit ratio for continuing the trial.

Any action that results in a temporary or permanent suspension of the trial will be reported as soon as possible by the investigators to the MUSC IRB and DSMB. If the DSMB or IRB requests a temporary or permanent suspension of the trial, they will notify the principal investigator who will promptly notify all co-investigators and the study team. Annually, the principal investigator and study coordinator will meet for data verification and protocol compliance checks. Specifically, these individuals will monitor whether all enrolled subjects met entry criteria, whether any deviations from the study protocol occurred, and whether any patients were prematurely removed from the protocol by managing physicians or withdrawal of parental consent. The principal investigator or study coordinator will review all CRFs and data within the study database for completeness and accuracy on an annual basis.

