### Study population

Five patients in need of a heart valve replacement will be included in the study. A study investigator who normally participates in our biweekly pediatric heart center case conference meeting and has access to patient records and surgical referrals for valve replacement will identify potential candidates for the trial. Study investigators will obtain permission from the primary cardiologist or cardiac surgeon prior to approaching parents or legal guardians to discuss participation in the trial. Telemedicine may be utilized to initially discuss the risks and benefits associated with the study with parents or legal guardians of potential subjects who are outpatients, but an in-person meeting will be required for a formal consent discussion. Expectant mothers who are carrying fetuses that are expected to require heart surgery requiring a valve replacement within the first two years of life may be approached for enrollment in the study as well.

The interventional portion of the study will take place in the cardiac operating rooms and in the Pediatric Cardiac Intensive Care Unit at Shawn Jenkins Children’s Hospital at MUSC. Additional observational data will be collected pre- and intraoperatively, and postoperatively on the Cardiac Stepdown Unit and in the outpatient cardiology clinics at MUSC’s Summey Medical Pavilion.

To be eligible to participate in this study, the patients can be either male or female and must meet the following inclusion and exclusion criteria:

Inclusion Criteria

Children less than 2 years of age who are referred for a cardiac operation that involves a primary semilunar valve replacement, or children less than 2 years of age who are referred for a cardiac operation involves an initial replacement of a previously placed prior homograft, bioprosthetic, or mechanical valve in the aortic or pulmonary positionDeemed acceptable for partial heart transplantation based on the standard evaluation process used for conventional orthotopic heart transplantation at our center (see S1 Appendix)Have insurance approvalProvide written informed consent of both parents or legal guardians; if there is only one parent or legal guardian, consent from that individual will be adequate.

Exclusion Criteria

Absolute contraindications for conventional orthotopic heart transplantation:

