#### Preoperative procedures

Written informed consent for partial heart transplantation will be obtained from the parents or legal guardians of each subject. Potential subjects and their parents or legal guardians will undergo a full evaluation for candidacy for partial heart transplant using well-established criteria and workflows for infants and young children who are being assessed for conventional heart transplantation. These patients will be listed for partial heart transplant using pre-established mechanisms similar to conventional heart transplantation via the regional South Carolina organ procurement network, We Are Sharing Hope.

For a subject to be enrolled in the trial, a time window will be established by an attending pediatric cardiologist as to how long the subject can be listed for partial heart transplantation before a conventional valve replacement option is scheduled. This time window will be determined based on the subject’s clinical status and severity of valve dysfunction and may be revised over time based on evolving clinical status.

As is the case for patients undergoing conventional heart transplantation, donor hearts will be selected based on the recipient’s ABO blood group, PRA, weight, CMV status, and EBV status. Parents or legal guardians of enrolled subjects will be required to carry a transplant pager, consistent with established practice for patients who are listed for conventional heart transplantation.

When a donor heart becomes available, a focused echocardiogram will be performed on the donor heart to specifically assess the semilunar valve annulus size and function before the heart is accepted. The donor heart will be procured and transported to MUSC by our cardiac surgeons using practices consistent with those utilized for conventional heart transplantation. The donor semilunar valve will be excised from the donor heart by a pediatric cardiac surgeon. The heart valve will be accepted after it is visually inspected by the procurement team at the donor hospital.

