### Data management methods

Data will be collected at intervals as described above. Descriptions of confidentiality provisions and data safety monitoring boards (DSMB) are provided in a later section. In order to preserve the confidentiality of the participants, the following interventions will be undertaken:

A. Case report forms (CRFs) will be developed prior to the onset of the trial and completed by a study investigator for each patient.
a. An enrollment form will be completed once written informed consent is provided by the parents or legal guardians.b. Adverse event forms will be completed as needed throughout the operative hospitalization.B. A dedicated Excel database will be developed for the trial.
a. All data from the CRFs will be entered into a dedicated Excel database by a study team member.C. In the case of a subject withdrawing from the trial, the data will be potentially included in the final analysis depending on the time enrolled in the trial.

Missing data will be addressed by omission or analysis as appropriate. Sensitivity analysis will be planned to avoid misleading inference when complete-case analysis is performed.

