### Assessment of results

The primary outcomes will be the feasibility and safety of partial heart transplantation. The feasibility will be determined by the ability to perform the new operation in at least one patient per year for three years after enrollment opens. The safety of the procedure will be indicated by survival and re-interventions that are the same or are better than those reported in the literature for patients of similar age undergoing conventional valve replacement. Safety will primarily be defined as patient survival or re-operation or transcatheter reintervention on the transplanted valve at six-month intervals, starting six months after the first subject undergoes a valve transplant, and continuing until one year after all five subjects have been enrolled. Safety will also be assessed by tracking rates of immunosuppression side effects, including development of insulin-dependent diabetes, chronic renal insufficiency, and significant infections.

The secondary outcomes will be valve annulus growth over time, stenosis and regurgitation. The valve annulus diameter will be measured using echocardiography in two planes at baseline and every six months following the operation. The valve annulus Z-score should remain relatively unchanged over time, indicating an increase in valve annulus growth corresponding with an increase in body surface area. This change should correspond to the growth of conventional heart transplants and Ross pulmonary autografts [18–20]. Valve stenosis and regurgitation will be assessed via transthoracic echocardiogram with pulse Doppler and with color Doppler, respectively, every six months following the operation.

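### The three early DSMB reviews are timed from enrolment, not transplant, so a review can hold no operative data on the child that triggered it

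*Protocol article*

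**What the plan says.** The DSMB schedule is in the protocol article under Confidentiality provisions: "The DSMB will meet virtually one month after each of the first three patients are enrolled and annually thereafter to review study data". The same section adds a meeting at the end of the study and meetings as needed for serious adverse events. The board reviews interim reports that summarise outcomes and adverse events, and after each meeting it advises on continuing, changing or ending the trial.

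What enrolment means has to be read from other sections:

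- Data management methods ties it to consent: "An enrollment form will be completed once written informed consent is provided by the parents or legal guardians".
- Preoperative procedures ties it to a waiting window: "For a subject to be enrolled in the trial, a time window will be established by an attending pediatric cardiologist", which states "how long the subject can be listed for partial heart transplantation before a conventional valve replacement option is scheduled". The window "may be revised over time based on evolving clinical status", and no maximum is given.
- Operative procedures provides for a cryopreserved homograft if the donor valve proves unsuitable.
- Assessment of results treats transplant and enrolment as different events. The safety outcome is assessed every six months, "starting six months after the first subject undergoes a valve transplant, and continuing until one year after all five subjects have been enrolled".

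The planned size is small: "Five patients in need of a heart valve replacement will be included in the study".

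**The concern.** The three early meetings appear intended to give an independent board a prompt look at a new operation, with immunosuppression, in children under two. That look is informative only if the child concerned has been operated on. With the clock starting at enrolment, whether there is anything operative to review depends on how soon a donor appears.

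Two things can go wrong. The meeting may fall while the child is still waiting, so that it has nothing on survival, reintervention or immunosuppression side effects for that child. Or the child may leave the list for a conventional valve, or receive a cryopreserved homograft, in which case one of only three early reviews has been used on a child without the study intervention. After the third early meeting, scheduled DSMB review is annual, so an operation that came after its own review may wait up to 12 months for the next scheduled look.

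**Working it through.** **Step 1. Order of events.** The article gives: consent and completion of the enrolment form (Data management methods); candidacy evaluation, listing and a waiting window (Preoperative procedures); donor offer; operation (Operative procedures). Whether enrolment is read as consent or as the setting of the window, it comes before the donor wait. The DSMB clock starts at enrolment and runs one month. No section ties a scheduled DSMB meeting to an operation. The only meetings that an operation's consequences can prompt are the as-needed ones for serious adverse events.

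**Step 2. Size.** The plan has no figure to reproduce, and it gives no waiting time. The following is an illustration on assumptions of mine: the time from enrolment to operation is exponential with median m months, and waits are independent between children.

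- Rate: λ = ln 2 / m.
- Chance that a child's own one-month review precedes that child's operation: p = exp(−λ × 1) = 2^(−1/m).
- Chance that this happens for at least one of the first three children: 1 − (1 − p)³.
- Chance that all three reviews precede any operation, with enrolments s months apart: the third review is at month 2s + 1, so the three children must wait longer than 2s + 1, s + 1 and 1 months. These sum to 3s + 3, which gives exp(−λ(3s + 3)).

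Worked example, m = 2: p = 2^(−0.5) = 0.707; at least one of three = 1 − 0.293³ = 0.975; all three with s = 0 = 2^(−1.5) = 0.354.

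| Median wait (months) | Own review precedes operation | At least one of three | All three precede any operation: enrolled together | 3 months apart | 12 months apart |
|---|---|---|---|---|---|
| 0.5 | 25% | 58% | 1.6% | <0.1% | <0.1% |
| 1 | 50% | 88% | 12.5% | <0.1% | <0.1% |
| 2 | 71% | 97% | 35% | 1.6% | <0.1% |
| 3 | 79% | 99% | 50% | 6.3% | <0.1% |
| 6 | 89% | >99% | 71% | 25% | 1.1% |

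The model leaves out children who exit to a conventional valve or a homograft. At a given transplant rate they can only raise the share of reviews without transplant data on the triggering child. When the donor does arrive within the month, the review still holds less than one month of postoperative data.

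**Step 3. After the change.** If the clock starts at transplant, the chance that a review precedes the triggering child's operation is 0 by construction, and each early review covers about one month after surgery.

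**The case against.** The strongest reply is that the board is not blind in the meantime. It meets as needed on serious adverse events. Its annual meetings are scheduled reviews of outcomes. The investigators meet every six months to weigh risk against benefit. Death or early reoperation would ordinarily be a serious adverse event and could reach the board without a scheduled meeting. An early meeting also has other business, such as recruitment and retention. All of this stands and lowers the stakes. It does not replace the early review, because as-needed meetings are reactive, annual ones may come late, and the six-monthly ones are not independent.

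A reader might also infer more than the article supports:

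- *That the early reviews will probably all precede the first operation.* This needs clustered enrolments or long waits. With enrolments 12 months apart it is about 1% or less for every median in the table, and later reviews would usually include earlier children's results.
- *That two of the five children go unreviewed because of this trigger.* They lack an early meeting because early meetings are limited to three patients. A transplant trigger for three would leave that unchanged, and those children remain under annual and as-needed review.
- *That the first operations could all escape scheduled review.* They would have to fall in one gap between annual meetings.
- *That children are enrolled before birth.* The article says only that expectant mothers "may be approached for enrollment in the study as well".

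**Conclusion.** The concern holds in a limited form. As written, the trigger allows an early DSMB review to contain no operative data on the child that prompted it, or to be used on a child who never has the study operation. That follows from the text alone. The size, 25% to 89% per child for median waits of 0.5 to 6 months, rests on an assumed exponential wait and shows a range, not a forecast. All three reviews preceding any operation is possible but extreme. If the authors used enrolled loosely to mean transplanted, the sentence conflicts with Preoperative procedures and Data management methods and still needs correcting. The other meetings soften the consequence, so this is a weakness in oversight that should be repaired, not a gap that leaves the trial unmonitored.

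**What to change.** In the DSMB paragraph, and in the charter if there is one, change the trigger to one month after each of the first three partial heart transplants. Keep the as-needed and end-of-study meetings. State that the annual meetings run from the start of enrolment, so that a long donor wait is still covered. Use enrolled throughout in the sense given in Preoperative procedures and Data management methods.

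The cost is a sentence or two. The number of early meetings stays at three. If the annual cycle was meant to begin only after the third early meeting, starting it with enrolment could add an occasional virtual meeting. The small drawback is that early meeting dates will depend on donor availability and cannot be fixed in advance.

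### DSMB reviews are timed from enrolment rather than transplantation, and nothing requires independent review of a death or lost valve before the next trial operation

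*Protocol article*

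**What the plan says.** All references are to the Protocol article.

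- **Size** (Study population): "Five patients in need of a heart valve replacement will be included in the study".
- **Scheduled independent review** (Confidentiality provisions): "The DSMB will meet virtually one month after each of the first three patients are enrolled and annually thereafter to review study data".
- **Unscheduled independent review** (same section): "The DSMB will also meet at the conclusion of the study, and as needed to review serious adverse events". No event, deadline or convener is given.
- **Investigators' own review** (same section): "The study investigators will meet every six months to review adverse events and to assess the risk/benefit ratio for continuing the trial". First-line surveillance is also theirs: "The study investigators will be primarily responsible for monitoring all study patients for the occurrence of adverse events and unanticipated problems as outlined above".
- **Suspension** (same section): the investigators report any action that suspends the trial to the IRB and DSMB as soon as possible. Separately, the DSMB or IRB may ask for suspension. No event is named that leads to it.
- **When enrolment is recorded** (Data management methods): "An enrollment form will be completed once written informed consent is provided by the parents or legal guardians".
- **Wait between listing and operation** (Preoperative procedures): individual, with no fixed length. "This time window will be determined based on the subject’s clinical status and severity of valve dysfunction and may be revised over time".
- **Start of the operation** (Operative procedures): it is scheduled as emergent, and the stated condition for starting is that the procurement team has inspected and accepted the donor valve.

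**The concern.** This is a new operation in children under two, and each result bears on whether the next child should have it. Independent review protects the next child only if it happens after the previous child's operation and before the next one. The article guarantees neither. The early meetings are tied to a date that may come before surgery, and later ones are tied to the calendar. The only event-driven route is discretionary, and it draws on data that the investigators collect and report. The plan could therefore be followed without deviation while a child is transplanted before the DSMB has considered an earlier death or valve loss.

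**Working it through.** The article gives no accrual rate, mortality or stopping boundary, so there is no stated figure to reproduce. The check is on timing. The illustrations below rest on assumptions marked as such.

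**1. Position of the one-month meeting relative to the operation.** Let w be the months from enrolment to transplant (not stated). The meeting falls 1 − w months after the operation:

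- w = 0: one month after.
- w = 1: at about the time of the operation.
- w = 3: two months before.

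Any wait longer than one month puts the meeting before that child's operation. Preoperative procedures also ties enrolment to setting the listing window, so enrolment comes before surgery on that reading too. Study population allows expectant mothers to be approached for enrolment, which could lengthen w further.

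**2. Does a scheduled meeting fall between consecutive operations?** Assume five operations spread evenly over 36 months, at months 0, 9, 18, 27 and 36 (36/4 = 9 months apart). Assume the same w for every child, and count annual meetings from the third early meeting. The early meetings fall at months 1 − w, 10 − w and 19 − w, and the annual ones at 31 − w, 43 − w and so on.

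| w (assumed) | Meetings at month | Pair of operations with no meeting between |
|---|---|---|
| 0 | 1, 10, 19, 31 | none |
| 3 | −2, 7, 16, 28 | third and fourth (18 to 27) |
| 5 | −4, 5, 14, 26, 38 | fourth and fifth (27 to 36) |

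If enrolment and operation coincide, every pair has a meeting between them. Even then, a death after that meeting and before the next operation has no scheduled review in between. Those stretches are months 1–9, 10–18, 19–27 and 31–36, or 8 + 8 + 8 + 5 = 29 of the 36 months. This is a share of calendar time, not a probability of death, because deaths may cluster soon after surgery.

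**3. Chance of another transplant before the next annual meeting.** The feasibility criterion in Assessment of results is "ability to perform the new operation in at least one patient per year for three years after enrollment opens". Take this as r = 1 operation a year at the low end and 5/3 = 1.67 at the high end. Assume Poisson arrivals and no ad hoc meeting.

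- Death at a random point in the 12-month cycle: 1 − (1 − e^(−r))/r = 0.368 at r = 1 and 0.513 at r = 1.67.
- Full 12 months remaining: 1 − e^(−r) = 0.632 and 0.811.

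These treat accrual as unlimited, whereas only two children remain after the third, so they are illustrative.

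**4. How often the situation could arise.** The event must occur in one of the first four children, since the fifth has no successor in the trial. With an assumed mortality p per child, 1 − (1 − p)^4 gives 19%, 34%, 59% and 76% for p = 5%, 10%, 20% and 30%. The article states no p.

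**5. What could force a review sooner.** The discretionary meeting and the suspension provisions both allow it. Neither says that a given event must be reviewed, by when, or that the next operation waits. The condition for starting surgery concerns only the donor valve.

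**The case against.** The strongest reply is that the route already exists. A death is plainly a serious adverse event, the DSMB may meet on it at once, and it is hard to imagine an external board of specialists leaving an infant's death in a five-patient trial until an annual meeting. This stands in part: prompt review is permitted and likely. It is not required, and no one is named to call the meeting.

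A second reply is that a DSMB charter or the full protocol may hold the trigger. It may, and neither is shown. But the article itself fixes the meeting dates, the board's remit and the handling of suspension. The criticism is of what it fixes, in particular the link to enrolment.

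A reader might also infer more than the text supports:

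- *That suspension can come only from the DSMB or IRB.* The article also provides for suspension arising otherwise, reported promptly to both.
- *That a death would wait 12 months.* That is the longest scheduled gap, and only if no ad hoc meeting is held.
- *That a 9-month spacing against a 12-month interval means the next child is usually operated on before review.* Under even spacing with no wait, a scheduled meeting falls between every pair. The comparison holds only for an event just after an annual meeting, and 36 months comes from a feasibility minimum, not an accrual plan.
- *That two of five children (40%) lose protection for a successor.* The fifth child has none in the trial.

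**Conclusion.** The concern holds as a gap in required timing. The per-patient DSMB reviews run from a date that can precede the operation, and they stop after the third child. Nothing obliges independent review of a death or loss of a transplanted valve before the next trial transplant. The documents do not show that such a review would fail to happen.

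The textual conclusion needs no numerical assumption. Its practical size does. The 37% to 51% and 63% to 81% figures rest on assumed accrual, Poisson arrivals and no ad hoc meeting, and the 12-month and 9-month figures are worst-case illustrations. An amendment is justified because the protection is cheap and the population is vulnerable, not because any one of these percentages is firm.

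**What to change.** Amend the DSMB text in three respects.

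1. Time the per-patient meetings from transplantation instead of enrolment, and extend them to the fourth patient, so that each of the first four is reviewed before the next trial operation. Copying the present enrolment-based meeting to later patients would not achieve this.
2. State that a primary safety event already listed in Assessment of results convenes the DSMB automatically. The events meant are death, and reoperation or reintervention that replaces the transplanted valve.
3. State that the DSMB's written recommendation on continuation, which the article already requires after every meeting, is obtained before the next trial transplant.

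The management of listed children meanwhile stays with the provisions in Preoperative procedures and the clinical team, and no clinical rule is proposed here.

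The cost is a short amendment, a few more virtual meetings and a possible missed donor offer while a review is pending. At 1 to 1.67 operations a year, the chance that the next operation would have fallen within one month of the last is 1 − e^(−r/12), or 8% to 13%, so waiting for a one-month meeting should seldom delay anyone. An event-driven review held promptly would add little to that.
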